## **PROTOCOL AND PROJECT DESIGN: EFFECTS OF A FUNCTIONAL REHABILITATION AND ENVIRONMENTAL ADAPTATION PROGRAM ON DEPENDENCY LEVELS, DYSPNEA, FUNCTIONAL CAPACITY, QUALITY OF LIFE, AND CAREGIVER BURDEN IN CANCER PATIENTS WITH ASSOCIATED RESPIRATORY PATHOLOGY: STUDY PROTOCOL**

In recent years, advances in cancer treatments, along with a strong focus on preventive strategies, have led to earlier diagnosis and improved understanding of oncological diseases, significantly increasing survival rates for cancer patients. As a result, the concept of "long-term survivor" has become increasingly important.

With this increase in survival and the subsequent rise in treatment lines, more side effects negatively impact aspects such as functionality and quality of life in patients. Some of these effects may include cancer-related fatigue, anxiety, or associated respiratory pathologies like dyspnea. Dyspnea, in particular, can present a significant health issue, with considerable limitations for individuals. In some patients with advanced cancer, dyspnea may be a clinical sign characteristic of the final stages of the disease. Approximately 41% of palliative care patients experience dyspnea, with 46% of them describing its intensity as moderate to severe. Moreover, the incidence of dyspnea increases considerably in patients with histopathological diagnoses of lung cancer, with studies reporting incidences higher than 73%.

Most patients perceive dyspnea as an uncontrollable limiting factor that leads to avoidance behaviors, increasing inactivity. This, in turn, negatively impacts their functionality, creating fear/avoidance patterns toward movement in cancer patients, similar to those seen in patients with chronic pain, chronic fatigue syndrome, or fibromyalgia. Patients with respiratory problems adapt to their symptoms by reducing activity levels, worsening their physical condition and exertion-related dyspnea, a phenomenon known as the "respiratory patient cycle."

To manage this, conventional clinical practice measures are typically implemented, primarily from a pharmacological perspective. However, we believe these measures are insufficient for achieving optimal symptom control. Despite current pharmacological treatments, the main symptom of respiratory pathologies—dyspnea—is not always adequately controlled, possibly due to its multifactorial nature. Most patients perceive dyspnea as an uncontrollable symptom, leading to avoidance behaviors that further reduce their activity levels, negatively impacting their functionality. Therefore, from an integrated care perspective, focusing not only on the symptom but on the patient as a whole, we have observed the necessity of employing additional interventions to help patients readjust to daily activities.

We have observed that cancer patients with respiratory pathologies adapt to their symptoms by reducing activity levels, leading to a worsening of physical condition and exertional dyspnea. This progressive inability results in loss of mobility, self-esteem, work capacity, and social relationships.

These data demonstrate that associated respiratory pathology is a common and often underestimated problem in oncology. It has been observed that individuals in this situation struggle to normalize their daily lives, either due to clinical deterioration or difficulty in applying what they learned during their hospital stay.

Regarding intervention measures, the NCCN panel highlights the importance of educational measures and energy conservation techniques as fundamental components of a comprehensive functional rehabilitation program. In addition to educational measures, the NCCN panel recommends the prescription of energy conservation techniques as useful for managing

associated respiratory pathology. This panel analyzes, on the one hand, a multicenter clinical trial involving 296 patients currently undergoing active treatment, which reported a decrease in symptom intensity after applying the program. On the other hand, they present a meta-analysis of 113 studies, with a total sample of 11,525 patients, showing improvements in patients following the use of non-pharmacological measures to manage associated respiratory pathology.

The frequent presence of associated respiratory pathology in cancer patients can lead to alterations in body composition, such as loss of muscle mass or increased visceral fat. Non-pharmacological interventions have proven to be an important tool for improving symptoms and some body composition parameters. In a study by Madison and colleagues, they observed a decrease in body fat after 12 weeks of moderate physical activity (bioelectrical impedance) in colorectal cancer survivors. Another study showed that an 8-week physical exercise intervention increased skeletal muscle mass and reduced visceral fat in a group of head and neck cancer patients undergoing chemotherapy. Fernández-Lao and colleagues demonstrated that a multimodal physical exercise program in breast cancer patients resulted in reduced body fat and increased lean body mass in a group of breast cancer patients. However, despite their potential benefits, there is little available evidence on functional rehabilitation interventions that have evaluated the effects on body composition in patients with associated respiratory pathology.

Scientific evidence and recent conclusions from expert meetings on cancer and the benefits of psychosocial interventions, both in prevention and treatment of various clinical aspects in cancer survivors or patients undergoing treatment, indicate sufficient evidence to support their efficacy in addressing physical function, fatigue, quality of life, pain, anxiety, and depressive symptoms, among others, associated with cancer.

Psychosocial non-pharmacological interventions have demonstrated effectiveness in managing these associated symptoms, even surpassing pharmacological interventions. This leads us to consider the biopsychosocial approach and multidisciplinary intervention (oncology, nursing, physiotherapy, occupational therapy, and medicine) as the global context for the intervention. Therefore, it is also essential to assess and intervene in aspects related to loss of function and pain associated with fear-avoidance disorders, which can be evaluated through degrees of kinesiophobia.

The cognitive-behavioral model of fear of movement suggests that patients with chronic pain or fatigue syndrome tend to avoid activity, believing it to be the cause of symptoms like pain and fatigue. Avoidance behavior leads to increased fear and more severe symptoms, resulting in more pain or fatigue. This concept can be extended to patients with associated respiratory pathology, making it important to restore optimal activity levels and prevent the loss of physical functions and capacities.

The selection of the most appropriate intervention setting depends on the clinical complexity and the patient's ability to self-manage their condition. Therefore, with expert support, our study proposes a supervised home-based intervention after hospital discharge, tailored to the specific circumstances of patients with associated respiratory pathology who have just been discharged. This aligns with recommendations for providing better access and adherence opportunities for these patients to a functional rehabilitation program.

Supervised follow-up outside the healthcare setting, both in the community and at home, has shown positive results in various previous studies. A meta-analysis of 14 randomized controlled trials in breast cancer survivors with telephone or email-supervised intervention showed good

outcomes. Regardless of the home-based setting, which is chosen for its feasibility in our study population, supervised and controlled follow-up of the intervention remains key to achieving positive results.

The best outcomes in cancer survivors or patients undergoing treatment have been achieved with multimodal physical exercise programs that combine various types of exercises, primarily aerobic activities and strength training, in addition to other interventions such as re-education in daily living activities and health education, which will be adapted to the patient's general condition and functional capacities. Therefore, we propose incorporating an interdisciplinary intervention, carried out by occupational therapists, nurses, physiotherapists, and medical specialists, aiming to improve conventional clinical practice and introduce a functional rehabilitation and environmental adaptation program that supplements conventional clinical practice. This is considered an essential intervention for the follow-up of patients with associated respiratory pathology after being discharged from their hospital stay.

### **5.2.2 PRACTICAL UTILITY AND POTENTIAL TRANSFERABILITY OF PROJECT RESULTS TO CLINICAL PRACTICE IN RELATION TO HEALTH**

As mentioned earlier, associated respiratory pathology is one of the most common symptoms related to cancer and its treatment, considered one of the most enduring symptoms with the greatest impact on quality of life. Therefore, the results of this study could be quickly integrated into the care process for patients with this symptomatology, with the goal of normalizing their daily lives. This research project is part of the regional research and innovation strategy for smart specialization (RIS3) of Castilla y León, which sets its thematic priorities in health and social care, demographic change, and well-being, aiming to improve the quality of life for citizens by researching new strategies that facilitate independent living for chronically ill and/or dependent individuals at home. The proposed intervention includes professionals from various healthcare levels, forming a multidisciplinary team that would support the development and implementation of the intervention.

The intervention will be carried out without overloading the in-hospital clinical practice, achieving a dual benefit. On the one hand, the patient will continue their rehabilitation intervention with reduced exposure and risk of infections or overburdening their environment. On the other hand, the hospital will benefit from an effective intervention outside the care center, which is currently overburdened due to multifactorial causes.

### **AIM**

**HYPOTHESIS:** Functional rehabilitation and environmental adaptation programs improve fatigue, pain, functional capacity, and quality of life in cancer patients with associated respiratory pathology.

**OBJECTIVES:** The primary objective of the study is to evaluate the effects of a functional rehabilitation and environmental adaptation program on the improvement of autonomy in cancer patients with associated respiratory pathology.

The secondary objectives are as follows:

1. Evaluate the effect of a functional rehabilitation and environmental adaptation program on activities of daily living, attention, executive functions, and quality of life parameters in cancer patients with associated respiratory pathology.

2. Assess the effect of a functional rehabilitation and environmental adaptation program on physical parameters in cancer patients with associated respiratory pathology, such as fatigue, pain, functional capacity, and body composition.
3. Describe if there is a correlation between levels of associated respiratory pathology and dependency levels in individuals.
4. Describe if there is a correlation between levels of dependency and kinesophobia levels in individuals.
5. Determine if there is a difference in terms of efficacy based on the oncological pathoanatomical diagnosis.

---

## **MATERIAL AND METHODS**

**DESIGN AND SETTING OF THE STUDY:** Design: A randomized, stratified, prospective, longitudinal clinical trial with a fixed parallel assignment scheme of an experimental group and a control group.

**SAMPLE/PARTICIPANTS:** Participants: The reference population consists of cancer patients with associated respiratory pathology hospitalized at the time of inclusion. The study population will be selected through consecutive sampling with the following selection criteria.

**STUDY SETTING:** The study will be carried out in a mixed setting between specialized care at the University Hospital of Salamanca (CAUSA) (Medical Oncology Department) and the University of Salamanca (Occupational Therapy Teaching and Assistance Unit, UDATO).

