#### **WITHDRAWAL CRITERIA:**

- Patient's death.
- Disease progression leading to a terminal state.
- Hospitalization at the time of home follow-up.
- Incomplete final assessment.

**Randomization:** Patients in the study population, after the initial interview with the research team and having met the selection criteria, will be randomly assigned to two groups: an intervention group (IG) and a control group (CG). The allocation sequence will be generated by

an independent researcher using the Epidat 4.2 software, with a 1:1 ratio. Participants will be randomized based on the order of their baseline assessment, and the randomization sequence will remain concealed until each patient is assigned to the appropriate group.

**Blinding:** The sequence, randomization, recruitment, and assignment work for each group (experimental or control) will be completed by research staff not involved in the evaluations or interventions, preventing potential biases in the study. Participants will also be blinded and unaware of the group to which they are assigned and the intervention they will receive. External research personnel trained in evaluation procedures will be incorporated to minimize any contamination between groups, ensuring third-party blind assessment. Additionally, the researchers responsible for the statistical analysis will be blinded, increasing the scientific rigor and quality of the study.

**Sample size:** The sample size estimation is based on the potential modification of one of the study's primary variables, the Barthel Index score. A pilot study with a similar population was used as a reference, where the Barthel Index score changed by 5.8 points. With these premises, accepting an alpha risk of 0.05 and a beta risk of 0.2 in a bilateral contrast, 40 subjects in each group are required to detect a difference of at least 5.8 units. A common standard deviation of 8.7 is assumed. A follow-up loss rate of 10% has been estimated. The sample size calculation was performed with the EPIDAT 4.2 software.

---

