The statistical analysis will be conducted by intention-to-treat. Population characteristics will be presented as means and standard deviations for continuous variables and as frequency distributions for qualitative variables. To evaluate comparability at baseline between the two study groups, the Chi-Square test will be used for qualitative variables, and the Student's t-test will be used for comparing means between the two groups. The effect of the intervention on the study variables will be assessed using a repeated measures ANOVA with two study factors (time \* group). Subgroup analyses will be performed considering certain baseline evaluation variables and/or categories, such as age or initial score on the FACT scale. Hypothesis testing will have an alpha risk of 0.05 as the statistical significance threshold. The statistical software used will be SPSS, version 23.0.

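### The trial is labelled stratified, but the randomisation names no stratum and the efficacy model contains none; the sections must be reconciled and the primary model set to match

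*Protocol*

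**What the plan says.** Under Material and methods, the design paragraph describes "A randomized, stratified, prospective, longitudinal clinical trial with a fixed parallel assignment scheme". No section names a stratification factor, its levels or a list per stratum.

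The Randomization paragraph says that the sequence is generated by "an independent researcher using the Epidat 4.2 software, with a 1:1 ratio". It adds: "Participants will be randomized based on the order of their baseline assessment, and the randomization sequence will remain concealed" until assignment. It refers to one sequence and mentions neither strata nor blocks.

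The efficacy analysis appears in Data analysis and again, almost word for word, in Statistical analysis: "The effect of the intervention on the study variables will be assessed using a repeated measures ANOVA with two study factors", those factors being time and group. Neither section has a stratum term, a baseline covariate or a diagnosis term. On subgroups, Data analysis says: "Subgroup analyses will be performed considering certain baseline evaluation variables and/or categories, such as age"; the only other example given is the initial FACT score.

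Secondary objective 5 under Aim is to "Determine if there is a difference in terms of efficacy based on the oncological pathoanatomical diagnosis".

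**The concern.** The design paragraph claims a property that the operative randomisation text does not deliver and that the analysis does not use. Whoever builds the Epidat list cannot tell from the protocol whether to build one list or several. The protocol says that the trial follows CONSORT, so the eventual report must describe the allocation as it was done, and the two sections give different starting points for that description.

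The analysis is affected whichever section is right. If allocation is stratified by something that predicts Barthel outcome, a model without that factor leaves between-stratum variation in the error term, and the reported standard error is too large. If allocation is not stratified, nothing in the design balances prognostic factors beyond chance, and a model with only time and group gives up precision that covariates already on file could supply.

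Objective 5 is a lesser, separate matter: it is the only objective that asks about a difference in effect between patient groups, and diagnosis is not among the subgroup examples.

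**Working it through.** **1. The plan's own figure.** Inputs from the Sample size paragraph: difference 5.8, SD 8.7, two-sided alpha 0.05, power 0.80, loss 10%.

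- n per group = 2 × (1.96 + 0.842)² × (8.7/5.8)² = 2 × 7.85 × 2.25 = 35.3, rounded up to 36.
- Allowing for loss: 36 / 0.90 = 40.

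The stated 40 per group is reproduced. With 36 evaluable per arm, SE = 8.7 × √(2/36) = 2.05 and power = Φ(5.8/2.05 − 1.96) = 0.81. Naming or removing strata does not change this calculation.

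**2. The sections side by side.**

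- Design paragraph: stratified, factor not named.
- Randomization paragraph: a sequence at 1:1, followed in order of baseline assessment, no factor.
- Data analysis and Statistical analysis: time and group only.

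If the design paragraph is right, the other two are incomplete. If the Randomization paragraph is complete, the label is wrong. No reading makes all three complete and consistent.

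**3. Cost of omitting a real stratum.** Let R² be the share of the variance of the compared quantity that the stratum explains. The SE from a model without the stratum is too large by a factor 1/√(1 − R²). The protocol gives no R², so these values are assumed:

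- R² = 5%: 1/√0.95 = 1.026, so 2.6% too large (2.05 against 2.00).
- R² = 10%: 1/√0.90 = 1.054, so 5.4% too large (2.05 against 1.95).

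The error is conservative. In a time-by-group test the compared quantity is change over time. A stratum that shifts every visit equally therefore costs nothing; only one that predicts change does.

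**4. Gain from covariates if there is no stratum.** With equal variances and correlation ρ between baseline and follow-up Barthel, a comparison of change has variance proportional to 2(1 − ρ), and one adjusted for baseline to 1 − ρ². The ratio is (1 + ρ)/2, which is below 1 for any ρ below 1. The protocol gives no ρ, so no figure is put on the gain.

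**5. Chance imbalance without stratification (illustration).** Take 80 patients, 40 per arm, K of them in a diagnosis group, with the number in one arm following Hypergeometric(80, K, 40). The probability that the arms differ by 20 percentage points or more is about 5% at an assumed prevalence of 20% (K = 16), 9% at 30% (K = 24), 11% at 40% (K = 32) and 12% at 50% (K = 40). The protocol gives no tumour mix.

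**6. Objective 5 (illustration).** Assume two diagnosis groups and 36 evaluable per arm. The interaction SE is 8.7 × √(2/n1 + 2/n2), where n1 and n2 are patients per arm in each group.

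- Equal split (18 and 18): SE = 8.7 × √(4/18) = 4.10; power for a 5.8-point interaction = Φ(5.8/4.10 − 1.96) = 0.29. The interaction detectable with 80% power is about 11.5 points.
- 30/70 split: power 25%, detectable 12.5 points.
- 20/80 split: power 20%, detectable 14.4 points.

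Separate tests would mislead. If the true effect is 5.8 in both halves, each test has SE = 8.7 × √(2/18) = 2.90 and power Φ(5.8/2.90 − 1.96) = 0.52. The chance that exactly one is significant is 2 × 0.52 × 0.48, or about 50%, with no true difference between diagnoses.

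**The case against.** The strongest reply is that this is missing detail and not a proven contradiction. The Randomization paragraph never says that allocation is unstratified, and patients can be taken in order of assessment within strata as well as overall. This stands: a single unstratified list is an inference from the wording. It does not remove the need to reconcile, because allocation has to be settled before the first patient is randomised and the paragraph that sets it out has no stratum.

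A reader might also infer that diagnosis is the intended factor and that objective 5 fails without stratifying on it. The documents support neither step. No section links the label to diagnosis, and a subgroup comparison is valid without stratified allocation. The Introduction ties lung cancer to dyspnea, which is a secondary outcome, and not to change in Barthel.

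Nor can it be said that diagnosis will go unanalysed. The subgroup list is open, and a statistical analysis plan, not seen here, may complete it. All that can be said is that the protocol states no analysis by diagnosis. It also does not say that separate tests are planned.

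Finally, the 29% interaction power is a consequence of trial size. Stratifying would leave it where it is, so it is a reason to label the result exploratory and no evidence of harm from the missing stratum.

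**Conclusion.** The point holds in a limited form. The protocol calls the trial stratified, describes allocation without a factor, and analyses with time and group only; these sections must be made to agree and the primary model must follow. The effect is modest: an SE 2.6% to 5.4% too large if a real stratum explaining an assumed 5% to 10% of variance is omitted, or an unquantified loss of precision if there is no stratum and no covariate is used.

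Two stronger conclusions do not follow. The between-group comparison is not biased under either reading, since chance imbalance under randomisation costs balance and precision, not validity. The sample size of 40 per group is not in question. The imbalance and interaction figures rest on assumed diagnosis splits, and the interaction figures also on the plan's SD of 8.7.

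**What to change.** Decide which section describes the allocation; if a list already exists, the list decides.

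- **If allocation is stratified:** name the factor(s) and levels in the Randomization paragraph and include them in the primary model, with their interaction with time if the repeated measures form is kept. Diagnosis group (for example lung/thoracic versus other) is one possible factor, not one that the protocol states.
- **If it is not stratified:** delete the word from the design paragraph. Adjust the primary analysis for baseline Barthel, used as a covariate and not also as an outcome level, and for diagnosis group as a prespecified covariate.
- **Objective 5, side note:** define the diagnosis groups and report one diagnosis-by-group interaction estimate with a 95% confidence interval, labelled exploratory, in place of separate tests.

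The cost is one edit to the text and one or two model terms, using data already collected at baseline, with no change to the sample size. Introducing stratification where none exists would need a new list and is cheap only before enrolment starts.
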